### Trial oversight and management

The trial will be overseen by a Steering Committee and a Management Committee. It will be managed by George Clinical: a Contract Research Organisation that has been commissioned on behalf of the sponsor to oversee the management of the trial.

### Site monitoring

Trial monitoring of the Australian sites will be performed by staff from George Clinical and by local monitors for sites outside Australia as specified in a detailed clinical trial monitoring plan.

### Data monitoring

An independent Data Monitoring Committee (DMC) will meet at least once per year to monitor the safety of trial participants and the quality of trial data. The DMC will be responsible for safeguarding interests of trial participants and protecting the integrity of the trial. The responsibilities and procedures of the DMC are detailed in a DMC Charter [53]. The DMC will conduct an unblinded interim analysis of efficacy and safety endpoints once 110 participants have completed the trial. The investigators and trial staff will remain blinded to the results of the interim analysis. The DMC may recommend continuing the trial, stopping the trial early, or modifying the trial. A recommendation to stop the trial early will be made only if there is clear evidence of a clinically important beneficial or harmful effect. The trial will not be stopped early on the grounds of futility.

### Adverse and serious adverse events

All participants will be screened weekly during the 10-week intervention period for adverse and serious adverse events. These will be reported to the lead Human Research Ethics Committee, Governance Office and sponsor as per local requirements. A serious adverse event is defined as any event that results in death, is life-threatening, requires inpatient hospitalisation or prolongation of existing hospitalisation, or results in a persistent or significant disability or incapacity. An adverse event is any untoward or unfavourable medical occurrence regardless of whether it is considered to be related to the participant’s involvement in the trial. However, adverse events that are highly prevalent in people with recent SCI and are unlikely to be related to the intervention (i.e., expected occurrences) will not be reported. These include urinary incontinence, urinary tract infection, respiratory infection and bowel incontinence (a full list of expected occurrences that will not be reported and as approved by the lead Human Research Ethics Committee is provided in the full protocol).

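### The exemption of expected occurrences from reporting has no seriousness limit, and the article does not say whether it or the serious adverse event definition prevails

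*Protocol article*

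**What the plan says.** All of the reporting rules stand in one paragraph of the Protocol article, Adverse and serious adverse events.

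- Screening: "All participants will be screened weekly during the 10-week intervention period for adverse and serious adverse events".
- Recipients: "These will be reported to the lead Human Research Ethics Committee, Governance Office and sponsor as per local requirements".
- Seriousness: "A serious adverse event is defined as any event that results in death, is life-threatening, requires inpatient hospitalisation or prolongation of existing hospitalisation". Persistent or significant disability or incapacity completes the list.
- Adverse event: "An adverse event is any untoward or unfavourable medical occurrence regardless of whether it is considered to be related to the participant’s involvement in the" [study].
- Exemption: adverse events that are very common after recent injury and "unlikely to be related to the intervention (i.e., expected occurrences) will not be reported".
- Named types: "These include urinary incontinence, urinary tract infection, respiratory infection and bowel incontinence". The complete list, approved by the lead ethics committee, is left to the full protocol.

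Under Data monitoring: "The DMC will conduct an unblinded interim analysis of efficacy and safety endpoints", once 110 participants have completed the trial. The DMC's procedures are left to its Charter.

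**The concern.** The exemption is defined by type of event, and two of the four named types are infections, which can be trivial or fatal. Nothing in the sentence or the list restricts it to the milder forms. A site following it literally could decide that a severe chest infection need not be reported because respiratory infection is on the list. Another site could report the same event because it met a seriousness criterion. With 15 hospitals in seven countries, serious infections could be counted differently from place to place.

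Two things are at stake. The first is oversight of individual serious events by the ethics committee, governance office and sponsor. The second is the comparison of arms. The exemption rests on a prior view that these types are unlikely to be caused by training. Whether 12 extra hours of training a week changes the rate of a common illness is something a randomised comparison can address. Judging causality case by case is least reliable when the background rate is high, so for serious events the count by arm is the more informative evidence.

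**Working it through.** No figure in the document bears on this point, so there is nothing to recompute. The check is to apply the stated rules, in order, to one event: a life-threatening respiratory infection in week 5.

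1. Is it detected? Yes. Week 5 lies within the 10-week screening period, which covers both arms.
2. Is it serious? Yes. The definition covers any event that is life-threatening ("A serious adverse event is defined as any event that results in death, is life-threatening") and makes no exception for expected types.
3. Is it also an adverse event? Yes. That definition takes in every untoward medical occurrence and sets no upper limit on seriousness, so serious events lie inside it.
4. Does the general rule require a report? Yes. The sentence on recipients follows directly on the screening sentence, which names both classes.
5. Does the exemption apply? Read literally, yes. It covers adverse events, opens with a word of contrast to what precedes it, and lists respiratory infection by type with no grade or seriousness limit.
6. Which of steps 4 and 5 prevails? The paragraph does not say. No sentence states that serious events are always reported, and none states that the exemption stops at non-serious events.

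The conflict is not confined to rare, extreme cases. Participants are eligible only if they are likely to stay in hospital for the next 10 weeks (Table 1, inclusion criterion 5), so prolongation of an existing stay is a seriousness criterion that an infection could readily meet.

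For the DMC, the reporting paragraph names three recipients: ethics committee, governance office and sponsor. The Data monitoring section gives the DMC an unblinded analysis of safety endpoints but does not say where those data come from or whether exempt events are included. The article therefore shows no route for such events to reach the DMC. It does not say that there is none.

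**The case against.** The strongest reply is that the paragraph keeps the two classes apart. The heading and the screening sentence name adverse events and serious adverse events separately, each has its own definition, and the exemption mentions only adverse events, directly after that definition. Two of the four examples are incontinence, plainly routine. One can also argue that a life-threatening infection is not a highly prevalent event and so fails the exemption's own condition. On this reading serious events stay reportable. It is a fair reading and may be what was meant. What stands of it is that the text is ambiguous; it does not remove the ambiguity, because the adverse event definition includes serious events and the list is by type.

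A second reply is that an article condenses the full protocol. That also has force: the full protocol may limit the list to non-serious events. But what the article expressly defers is the list of types. The exemption itself is printed as a rule, without a limit.

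Third, other data are compared by arm: time to discharge, survival to 6 months and re-hospitalisation in the economic evaluation, and therapy sessions missed through illness are recorded. An excess of deaths or long stays would leave some trace there. None of these identifies serious events by type.

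A reader might infer more than the documents support:

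- That the DMC would be unable to see an imbalance in infections. The paragraph governs reports to three named bodies; it does not say that exempt events go unrecorded or are withheld from the DMC, and the Charter is not shown.
- That the trial will claim no excess harm without the data to back it. The article makes no such claim.
- That a particular number of events would be lost. The article gives no infection rates, so any count would be invented.
- That exempting common non-serious events is itself an error. It is a design choice, with content approved by an ethics committee, made to limit reporting burden.

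**Conclusion.** The point holds as a conflict between two statements in one paragraph. An infection that is fatal, life-threatening or prolongs the stay is serious under one and exempt from reporting under the other, and the article does not rank them. The consequence is that sites could leave such an event unreported and could differ in doing so; that any site has done so is not shown.

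The size cannot be given in events. The conflict affects only events that are both of a listed type and serious, but those are the listed events that matter most for safety. The conclusion rests on the article's wording alone. If the full protocol already confines the exemption to non-serious events, or the Charter already gives the DMC all serious events by arm, what remains is to say so in the article. The change is worth making because it is cheap and concerns safety.

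**What to change.** Reconcile the two statements with one sentence, for example: *Expected occurrences are exempt from reporting only when they are not serious; any event that meets a seriousness criterion is reported whatever its type.* Add that these events are tabulated by arm for the DMC and in the final report. If the full protocol or the DMC Charter already provides this, cite it and confirm that sites apply it in that way.

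The cost is some additional serious adverse event reports, a notice to sites and, if the ethics-approved wording has to change, an amendment. By June 2023, 128 of 220 participants had been randomised, leaving 220 − 128 = 92 to come at that date. For those already enrolled, sites could be asked whether any serious event of a listed type was left unreported. No treatment, eligibility criterion or sample size changes. Collecting the non-serious listed events by arm is not needed to settle this point; it would be a separate choice, with its own burden in a trial already under way.

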## Discussion

The SCI-MT Trial when completed will be one of the largest non-pharmaceutical investigator driven trials of a rehabilitation intervention in people with recent SCI. If the intervention is found to be effective, the results will be of immediate and direct relevance for inpatient care. However, the future potential rollout of the intervention will rely on the cost as well as overcoming any real or perceived barriers. For this reason, a detailed economic analysis and process evaluation will run alongside the trial.

The SCI-MT Trial is pragmatic. Consequently, it aims to mimic how intensive motor training would be administered in the real world. Some participants may not receive the full additional 12 h per week of motor training for 10 weeks for reasons outside their and our control. The reasons for departures from the scheduled intervention will be carefully recorded and accepted as part of the real-world situation and treatment paradigm for our primary intention-to-treat analysis. This is in keeping with the standard approach for pragmatic trials [54–58]. While the trial is pragmatic, we will nonetheless use contemporary causal modelling approaches to estimate the Complier Average Causal Effect of the intervention (as described in the “Methods” section).

We anticipate some variability in usual care. This will not confound estimates of the effect of the intervention. However, time spent in training may mediate the treatment effect [51]. For this reason we will determine the extent to which the effects of the intervention are mediated by time spent in training.

As of June 2023, 128 participants have been randomised (with 7 participants randomised per month). If the current rate of recruitment continues, the trial will be fully recruited by the end of 2024, as planned. Nonetheless, one of the biggest barriers to the success of any trial is recruitment [59]. In anticipation of this problem, the trial involves many sites around the world. Each site is required to recruit between 5 and 11 participants per year. This is considered achievable. If the rate of recruitment per month drops for any reason, we will consider opening more sites.

The Early & Intensive SCI-MT Trial will provide the first, rigorous evidence of the impact of a treatment approach designed to promote neural recovery and improve motor function following SCI. Improved neurological recovery and motor function could have tangible, meaningful and potentially life-altering implications for people with SCI. The results of this trial could also direct future guidelines for the inpatient rehabilitation care of these people.

## Data Availability

This is a trial protocol so there is currently no data to share.
